### Data collection

To ensure that accurate, complete and reliable data are collected, the CTU will provide training to site staff in the format of investigator meetings and/or site-initiation visits. Data will be collected through electronic data capture (EDC). Data will be obtained through patient’s hospital notes, hospital laboratory records and image records. All data for an individual patient will be collected by the PI or their delegated nominees and recorded in the EDC database for the study except 90-day follow-up data. For the economic evaluation, HRQoL will be measured by the EQ-5D-5 L at baseline and at 90 days post surgery. Resource use data will be collected via the questionnaire administered at 90 days post surgery. The patients’ confidentiality will be maintained and will not be made publicly available to the extent permitted by the applicable laws and regulations. On completion of the trial, the trial master file will be archived by the CTU and the investigator site file and study data will be archived by the PI at each site according to the applicable regulatory requirements.

### Follow-up visits and procedures

All survivors will be followed up at 90 days after surgery. HRQoL will be measured using the EQ-5D-5 L administered at baseline and at 90 days post surgery. Health and social care resource use will be collected via a questionnaire at 90 days post surgery. Where the patient has been discharged from hospital, questionnaires will be administered via post. If questionnaires are not returned, a maximum of two telephone contacts will be made to the study participant; the first call will check that the questionnaire has been received and the participant is happy to complete it. If necessary, a second copy of the questionnaire will be sent. In the event of non-return, one further telephone contact will be made and the health economic data collected over the telephone where possible. To minimise the risk of causing distress by contacting relatives of patients who have since deceased, the CTU will contact the patient’s GP to ascertain the patient survival status prior to any contact being made.

### Safety monitoring and adverse event (AE) reporting

The AEs will be defined as stipulated by the Medicine and Healthcare Products Regulatory Agency (MHRA) Good Clinical Practice Guide 2012 and reported as per guidance. The PI or designee will record all directly observed AEs and those reported by the patient. In addition, the patient will be asked about AEs up to 28 days post surgery or on discharge from hospital if earlier. The PI or designee must assess all AEs for seriousness, causality, severity and if the AE is related to the study drug for expectedness. All reportable AEs should be recorded in the patient’s medical notes and on the AE form within the EDC.

Prevention HARP-2 is recruiting a population that is already undergoing a major surgical intervention, it is expected that many of the participants will experience AEs. Events that are expected in this population (i.e. events that are in keeping with the patient’s underlying medical or surgical condition) should not be reported as AEs or SAEs. Death which is ascertained to be not related to surgical complications or progression of the primary or secondary outcomes should be reported as a SAE. SAEs will be evaluated by the PI for causality (i.e. their relationship to study drug) and expectedness. An adverse reaction (AR) is an AE which is related to the administration of the study drug. If any AEs are related to the study drug (i.e. are ARs) they must be reported on the AE form within the EDC.

The following are ARs which are expected and must be reported on the AE form within the EDC: CK > 10 times the ULN, ALT/AST > 5 times the ULN.

The following serious adverse reaction is expected and must be reported on the SAE form within the Case Report Form (CRF): need for renal replacement therapy in patients with CK > 10 times the ULN.

All SAEs should be reported within 24 h of becoming aware of their occurrence. They should be reported to the CTU and the chief investigator (CI), who will inform the sponsor and regulatory authorities.

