#### Secondary outcomes

Secondary outcomes include clinical outcomes, safety and health economic outcomes (health-related quality of life (HRQoL) and costs).

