##### Safety

Creatine kinase > 10 times the ULN (day 0, day 3 and day 7 post surgery) of the local laboratory range; ALT/AST > 5 times the ULN (day 0, day 3 and day 7 post surgery) of the local laboratory range; acute kidney injury defined according to Kidney Disease Improving Global Outcomes guidelines (using change from baseline SrCr) within 7 days of surgery; SAEs, AEs and occurrence of suspected unexpected serious adverse reactions (SUSARs).

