### Trial organisation/oversight

Participant safety will be monitored by an independent Data Monitoring and Ethics Committee through regular review of AEs. A Trial Steering Committee will provide trial oversight. The members of the Committees will be experienced in clinical trials and will be from a variety of backgrounds including clinical trialists, a statistician and a lay public member. All protocol amendments will be implemented only after approval from the sponsor, Ethics Committee and MHRA. The trial will comply with the principles of GCP, the requirements and standards set out by the EU Directive 2001/20/EC and the applicable regulatory requirements in the UK, the Medicines for Human Use (Clinical Trials) Regulations 2004 and subsequent amendments and the Research Governance Framework. It will also adhere to the SOPs of the NICTU. The trial will be subject to independent audit initiated by the sponsor, MHRA and trial monitoring as per NICTU monitoring SOPs.

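### The death rule for SAE reporting exempts progression of any secondary outcome, and the secondary outcomes include the trial's own safety measures (CK, ALT/AST and acute kidney injury)

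*Protocol article*

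**What the plan says.** All of this is in the protocol article.

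- **Death rule** (Safety monitoring and adverse event (AE) reporting): "Death which is ascertained to be not related to surgical complications or progression of the primary or secondary outcomes" is to be reported as an SAE. Deaths that are related to those things are exempt by implication.
- **Expected events** (same section): events that fit the patient's disease or operation "should not be reported as AEs or SAEs".
- **Scope of the secondary outcomes** (Secondary outcomes): "Secondary outcomes include clinical outcomes, safety and health economic outcomes".
- **Safety outcomes** (Safety): "Creatine kinase > 10 times the ULN (day 0, day 3 and day 7 post surgery"), "ALT/AST > 5 times the ULN (day 0, day 3 and day 7 post surgery"), AKI by KDIGO criteria within 7 days of surgery, and "SAEs, AEs and occurrence of suspected unexpected serious adverse reactions (SUSARs"). Day-28 and day-90 mortality are listed under Clinical outcomes.
- **Adverse-reaction rules** (Safety monitoring): all AEs are assessed for seriousness and causality. Any AE related to study drug goes on the AE form. CK and ALT/AST rises above the same thresholds are expected adverse reactions and also go on the AE form. Renal replacement with CK above 10 times ULN is an expected serious adverse reaction and goes on the SAE form.
- **Timing and causality** (Safety monitoring): the 24-hour report and the investigator's evaluation of causality and expectedness are stated for SAEs.
- **Committee** (Trial organisation/oversight): "Participant safety will be monitored by an independent Data Monitoring and Ethics Committee through regular review of AEs".

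**The concern.** Exempting anticipated post-surgical events and efficacy outcomes from SAE reporting is a normal choice in a high-risk surgical trial, because it avoids reporting the same event twice. It depends on the exempt list holding only what the operation and the disease are expected to cause. Here the list is set by a general reference to the primary and secondary outcomes, and the secondary outcomes contain the measures chosen to detect harm from simvastatin.

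The exemption therefore turns on whether a death can be linked to surgery or to a listed outcome, not on whether it could be related to the drug. The filter also comes before the evaluation of causality and expectedness stated for SAEs. At stake is the prompt individual review of a possibly drug-related death, and the completeness of the SAE comparison between arms, which is itself a safety outcome.

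**Working it through.** The article states no figure on this point, so the check sets its sections side by side.

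**Step 1: which outcomes the exemption covers.** The death rule refers to the primary and secondary outcomes without restriction. The Secondary outcomes section includes safety, and the Safety section names CK, ALT/AST and AKI. Deaths from progression of any of these are inside the exemption as written.

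**Step 2: whether the literal scope can be what was meant.** Mortality is also a secondary outcome, and so are SAEs and AEs. If every listed item counts, every death is exempt and the rule does nothing. Some narrower list must have been intended, but the article does not give it.

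**Step 3: what each type of death triggers under the article's rules.**

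| Death following | Reported through other rules | The death as an SAE |
|---|---|---|
| CK > 10 x ULN, no renal replacement | CK rise on the AE form | Exempt as written |
| ALT/AST > 5 x ULN | Transaminase rise on the AE form | Exempt as written |
| Renal replacement with CK > 10 x ULN | Renal replacement on the SAE form, within 24 h | Exempt as written, but the SAE report already made stands |
| AKI, with neither high CK nor renal replacement, or with renal replacement alone | None, unless judged drug-related (then the AE form) | Exempt as written |
| ARDS, pulmonary complication or MI | None, unless judged drug-related (then the AE form) | Exempt; an ordinary efficacy-outcome exemption |

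**Step 4: the internal conflict.** In the first two rows the same section calls the underlying event an adverse reaction, and in the third a serious adverse reaction, yet the death rule treats a death from its progression as a non-SAE.

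**Step 5: the weakest row.** AKI is not among the adverse reactions that must be reported. After major surgery it can readily be judged to fit the operation, and the expected-events rule then keeps it off both forms. Only a drug attribution by a blinded investigator brings it back, and the rule for drug-related AEs names the AE form without attaching the 24-hour duty. Yet AKI is the one safety parameter that the Statistical analysis plan section names for the interim analysis.

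**The case against.** The strongest reply is that the literal reading is too literal. The paragraph is about events that fit the patient's condition, and progression suits ARDS, pulmonary complications, MI, AF and thromboembolism better than laboratory thresholds that the section separately declares reportable. The article also condenses a full protocol, which may list the exempt outcomes more narrowly. This makes loose drafting the likely cause, but the published sentence still gives an investigator no narrower list to apply.

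Three stronger readings are tempting, and the article does not support them.

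- *Drug-related deaths bypass the committee's AE review.* Not in general. CK and ALT/AST threshold events and every AE judged drug-related must be on the AE form, and the committee reviews AEs.
- *Renal replacement with high CK is reportable if the patient survives but exempt if the patient dies.* Nothing withdraws the SAE report for the renal replacement when death follows.
- *The committee sees deaths and other exempted events only at one interim analysis.* The article describes regular review and an interim that shows AKI with other safety data. It does not say that outcome or mortality data are withheld at other reviews.

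The data are not lost either. Mortality, the clinical outcomes, CK, ALT/AST and AKI are all collected as outcomes, so an excess on one arm could be seen there. That stands, and it limits the point to SAE status, the 24-hour route and the causality step. It does not replace them: a later comparison of outcomes is not a prompt causality assessment of an individual death.

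The instruction to record all observed AEs and the instruction not to report expected ones can be read together, since the section speaks of reportable AEs. No contradiction is claimed there.

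**Conclusion.** The point holds in a limited form. The death rule, read with the outcome definitions, takes deaths from monitored drug toxicities out of SAE status, out of the 24-hour report and out of the evaluation stated for SAEs. This conflicts with the adverse-reaction rules in the same section. The clearest exposure is a death following AKI, without the combination of CK above 10 times ULN and renal replacement, that a blinded investigator attributes to surgery. For CK and ALT/AST the loss is of SAE handling of the death, not of the AE record.

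No count is attached. The article gives no mortality rate and no basis for the share of deaths that would be exempt or drug-related, so any number would be a guess. The conclusion rests on the article's wording and on the assumption that the full protocol does not already narrow the exempt list. If it does, the remaining task is to bring the article's wording into line.

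**What to change.** Reconcile the death rule with the outcome sections:

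1. Replace the general reference to primary and secondary outcomes with a named list, limited to the primary outcome components and the clinical efficacy outcomes. Mortality itself should not be on it.
2. State that the safety outcomes (CK, ALT/AST and AKI), and deaths following them, are not exempt.
3. Require causality to be assessed for every death before any exemption applies.
4. Give the monitoring committee a by-arm tabulation of all deaths and all exempted serious events at its reviews.

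The cost is a wording amendment through the approvals the article already describes, a few more SAE reports and some extra tabulation. The events are already collected as outcomes, so no new data collection is needed.

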### Statistical analysis plan

This is a randomised, placebo-controlled, parallel-group, superiority trial. Intention-to-treat analysis (ITT) will be followed for the primary analysis and patients will be analysed according to the treatment that they were randomised to, disregarding the actual treatment received. Patients should have received at least one dose pre surgery for inclusion into the analysis. Patients who did not proceed to the planned surgery will also be excluded from the final analysis. A per-protocol analysis will be performed in addition to the ITT analysis.

The primary outcome measure will be compared between treatment groups using a chi-square test. We will also report each primary outcome component separately. A secondary analysis will involve a logistic regression model, with the dependent variable as composite endpoint/no composite endpoint within 7 days and the independent variables as treatment, centre, type of surgery and age as a covariate. An odds ratio measuring the treatment effect and its 95% confidence interval will be reported. Other categorical outcomes will be analysed using logistic regression models, with treatment group as an independent variable along with centre, type of surgery and age as a covariate. The summary statistics will be based on proportions and the 95% confidence interval. Continuous outcomes will be analysed using linear regression models, with treatment group as an independent variable and terms for centre, type of surgery and age in the model. Difference in treatment will be based on adjusted mean estimates and 95% confidence intervals. Time-to-event data will be analysed using a log-rank test. Any patients who have not experienced an event at the time point of interest or withdrawn will be censored. The proportion experiencing an event over time will be illustrated using a Kaplan-Meier curve for each of the treatment groups. The *p* values and a hazard ratio with its 95% confidence interval from a Cox proportional hazards model will also be presented. The proportional hazard assumption across treatment arms will be checked graphically using a log-cumulative hazard plot.

Baseline characteristics, follow-up measurements and safety data will be described using appropriate descriptive summary measures depending on the scale of measurement and distribution.

Subgroup analyses will use a statistical test for interaction and will be reported using 99% confidence interval. Four subgroup analyses are pre-specified, stratifying by chemotherapy prior to surgery (yes/no), type of surgery (oesophagectomy, lobectomy, pneumonectomy), surgical technique (minimally invasive/hybrid/open) and duration of OLV (≤ 120 min and > 120 min [20]). We shall also investigate subgroups based on smoking status.

An interim analysis will also be conducted to analyse efficacy and safety parameters. This will occur when approximately 50% of the planned number of patients to be randomised have completed day 28 assessment or have been discharged from hospital, whichever is sooner. In relation to efficacy, a chi-square test will be applied with a *p* value < 0.001 according to the Haybittle-Peto stopping rule. For safety, the acute kidney injury data will be presented alongside other safety data.

Every effort will be made to minimise missing baseline and outcome data in this trial. The level and pattern of the missing data in the baseline variables and outcomes will be established by forming appropriate tables and the likely causes of any missing data will be investigated. This information will be used to determine whether the level and type of missing data have the potential to introduce bias into the analysis results for the proposed statistical methods, or substantially reduce the precision of estimates related to treatment effects. If necessary, these issues will be dealt with using multiple imputation or Bayesian methods for missing data as appropriate. A detailed statistical analysis plan will be produced prior to the end of patient recruitment and database lock.

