##### Health economic outcomes

HRQoL as measured using the EuroQoL-5 Dimension Questionnaire (5-level version) (EQ-5D-5 L) [32] at baseline and at 90 days post surgery; health and social care resource use: length of ICU stay (level-3 care), length of high-dependency unit stay (level-2 care), length of hospital stay, health service contacts up to 90 days post surgery.

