### Health economic evaluation

A within-trial cost-utility analysis will be conducted to assess the cost-effectiveness of simvastatin compared to placebo at 90 days’ follow-up (post-surgery). A health service perspective will be adopted as recommended by the National Institute for Health and Care Excellence (NICE) [37]. The health outcome for the analysis will be quality-adjusted life years (QALYs) and these will be calculated for each patient using responses on the EQ-5D-5 L. Patient-level healthcare resource use (of primary, community and social care services) will be obtained from the trial CRF and the self-completed patient questionnaires, and combined with publicly available unit costs to estimate costs for each participant. It will not be necessary to discount costs and outcomes given the duration of follow-up. Standard methods will be used to explore and display uncertainty in the cost-effectiveness data including scatter plots on the cost-effectiveness plane and cost-effectiveness acceptability curves. Sensitivity analyses will be performed to assess the robustness of the cost-effectiveness results to changes in key parameters. A detailed health economic analysis plan will be finalised prior to commencing the analysis.

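### The stated linear model for continuous outcomes leaves out the baseline value, so the 90-day EQ-5D-5L comparison is less precise than the collected data allow

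*Protocol article*

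**What the plan says.** The Secondary outcomes section of the protocol article places quality of life among the trial's secondary outcomes: "Secondary outcomes include clinical outcomes, safety and health economic outcomes (health-related quality of life (HRQoL) and costs". Follow-up visits and procedures fixes the measurement times: "HRQoL will be measured using the EQ-5D-5 L administered at baseline and at 90 days post surgery". The Health economic outcomes section gives the same two times.

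For analysis, the Statistical analysis plan section states one model for all continuous outcomes: "Continuous outcomes will be analysed using linear regression models, with treatment group as an independent variable and terms for centre, type of surgery and age". It then says how the result is reported: "Difference in treatment will be based on adjusted mean estimates and 95% confidence intervals". Neither that section nor any other adds the baseline value of the outcome, and none specifies a change-from-baseline analysis for EQ-5D-5L.

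QALYs are treated separately, under Health economic evaluation. The article says only that "these will be calculated for each patient using responses on the EQ-5D-5 L", and closes that section with "A detailed health economic analysis plan will be finalised prior to commencing the analysis". For the trial as a whole it says: "A detailed statistical analysis plan will be produced prior to the end of patient recruitment and database lock".

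**The concern.** When an outcome is measured before treatment and again at follow-up, the baseline score usually explains part of the follow-up variation. Entering it as a covariate removes that part from the residual variance and corrects the estimate for whatever chance difference exists between the arms at baseline. Here the baseline score is collected, yet the covariates the article names are centre, type of surgery and age.

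This differs from silence. Had the article said nothing about covariates, the matter would belong to the detailed plan. It names them, and a plan that follows the list as written would leave baseline utility out. The cost would be a wider interval for a secondary outcome, from data the trial already holds. Precision at 90 days is likely to be scarce, because only survivors are followed up and those already discharged are sent postal questionnaires.

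**Working it through.** **Inputs from the protocol article.** EQ-5D-5L at baseline and 90 days; model terms treatment, centre, type of surgery and age; 1:1 allocation; 203 per arm before dropout.

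**Input not in the documents.** The correlation r between baseline and 90-day utility, given the other covariates. It is assumed here as 0.3, 0.5 and 0.7.

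**Step 1: the plan's own figure.** The only planning figure is for the composite primary outcome; none is given for EQ-5D-5L. With 25% against 12.5%, two-sided 5%, 90% power and a chi-square test without continuity correction:

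n = [1.960 × √(2 × 0.1875 × 0.8125) + 1.282 × √(0.25 × 0.75 + 0.125 × 0.875)]² / 0.125² ≈ 203 per arm

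Dropout: 203 / 0.9 = 225.6, so 226 per arm and 452 in total. This matches the article and does not depend on the present point.

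**Step 2: precision.** Adding baseline multiplies the residual variance by 1 − r². Leaving it out widens the 95% confidence interval by the factor 1/√(1 − r²). The number per arm that, with baseline, gives the precision of 203 per arm without it is 203 × (1 − r²).

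| Assumed r | Variance factor 1 − r² | CI wider without baseline | Equivalent to 203 per arm |
|---|---|---|---|
| 0.3 | 0.91 | 4.8% | 185 |
| 0.5 | 0.75 | 15.5% | 152 |
| 0.7 | 0.51 | 40.0% | 104 |

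The variance factor and the widening do not depend on the number analysed. The figure of 203 is only a yardstick, since the number with a 90-day questionnaire will probably be smaller.

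**Step 3: the same loss seen as imbalance.** With 203 per arm, the standard error of a chance baseline difference is √(2/203) = 0.099 SD, a 95% range of about ±0.19 SD. If the SDs at the two times are equal, a baseline difference of d SD moves the unadjusted 90-day difference by r × d. For d = 0.1 that is 0.03, 0.05 and 0.07 SD at r = 0.3, 0.5 and 0.7. This is not an extra error on top of Step 2. The unadjusted interval already allows for it, and that is why it is wider.

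**The case against.** **The model may not be meant for EQ-5D-5L.** The instrument is listed under health economic outcomes, and its only explicit analytic use is to form QALYs. The general sentence fits outcomes with no baseline value, such as ventilator-free days and length of stay. This has some force, but quality of life is named as a secondary outcome in its own right, and the article gives no other model for it. As written, the general sentence is the one that applies.

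**Details can wait for the later plan.** A detailed statistical analysis plan is promised, and the list is not said to be exhaustive. It may well add the baseline term. That makes this an easy improvement, not a defect that cannot be mended; it does not change what the article now states.

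**Nothing stated is invalid.** This stands. Under 1:1 randomisation the model without baseline gives an estimate that is unbiased in expectation (deaths and non-return at 90 days are a separate matter), with an interval that allows for chance imbalance. The point is efficiency on a secondary outcome with no stated power target.

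**A stronger reading about QALYs.** With only two measurements, a reader might infer that baseline imbalance passes into the QALY difference and can drive the cost-utility result. The documents do not support that. Nothing applies the continuous-outcome model to QALYs. The health economic section names no regression and defers to a plan that is not shown, which may adjust for baseline utility. Any figure for the effect would also need an assumed utility SD, correlation and method of interpolation, so none is offered here.

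**An extension to biomarkers.** A reader might also want the same rule for the plasma and urine markers. The Exploratory outcomes section gives no sampling times, so the article does not show that pre-treatment values exist.

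**Conclusion.** The point holds for the 90-day EQ-5D-5L comparison, as a free gain in precision that the stated model does not take. For r between 0.3 and 0.7, the confidence interval is about 5% to 40% wider than it need be, and about 15% wider at r = 0.5. These sizes rest on the assumed correlation and on reading the general model as the one for EQ-5D-5L. At the low end of the range the gain is small.

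The point does not show bias in the 90-day comparison or an error in the QALY analysis. It does not touch the primary outcome, its analysis or the sample size.

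**What to change.** Add one sentence to the Statistical analysis plan section, and carry it into the detailed statistical analysis plan: *continuous outcomes that also have a baseline measurement, namely EQ-5D-5L utility, will include that baseline value as a covariate alongside centre, type of surgery and age.*

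The health economic analysis plan should use the same baseline adjustment when it models QALYs. This is a request for consistency with a document not shown here.

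The cost is the sentence itself and one extra model parameter. The data are already collected, and missing baseline scores fall under the section's existing provisions for missing baseline data. It should be settled before database lock and unblinding, so that the adjustment is plainly pre-specified.
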